## **3.3 FOLLOW UP**

Participants will be followed-up until 90-days post operation.

## **3.4 INTERNAL PILOT**

There will be an internal pilot of feasibility after 9 months of recruitment, (beginning of funding month 7 to end of funding month 15)

In preparation for this application, a search of NHS England HES treatment episodes was undertaken, supplemented by searches of the National Cancer Registration and Analysis Service (26, 39). Treatment episode codes are available upon request. These figures were corroborated with available reports from the Colorectal Cancer Screening Programme. A total of about 270,000 procedures requiring EDPTP are undertaken each year within the NHS. This includes: ~121,410 hip replacements, 87,497 knee replacements, and 55,220 major abdominal / pelvic operations. This equates to 675,000 procedures undertaken across the active recruitment period, with our sample representing as few as 1.3% of cases performed across the UK.

From the feasibility analysis from sites, they stated that they would treat between 30–1000 overall potential participants requiring EDPTP each month. Based on a staggered set-up of approximately 50 sites over 13 months of the recruitment window, at a rate of 4 sites per month to reflect pragmatic trial set up, including 11 months of all sites recruiting at steady state and subsequent 90 days follow-up of the last participant, a total of 890 centre-months recruitment would be accumulated.

Recruiting at a rate of ~9.7 participants per active month per site would reach the sample size by the end of 24-month recruitment window.

By the end of the 9-month internal pilot we will have set up 36 sites and accumulated 166 centre months (assuming on average a site contributes half a month in the month they are set up). As detailed earlier, the 100% recruitment rate is 10 participants per site per month (which accounts for the staggered site set-up). This equates to a target of 1571 participants at the end of the 9-month internal pilot. Although 1571 is equivalent to 18.2% of the overall 8,608 participants, it is indicative that the trial is on track to meet 100% recruitment by the end of 24-month recruitment window (**Table 1**).

If trial recruitment was under target, there is the option to set up an extra 10 sites. A second staggered set-up from month 18 (allowing time from TSC meeting to then achieving confirmation of capacity and capability from local research and development units) of the additional 10 sites has been modelled amounting to 126 additional centre-months by the end of the 24-month window. We would consider stopping if we had less than 18 sites and consider adapting if we had between 18 and 35 sites.

In line with the NIHR-funded GAPS trial(18), we have set reasonable adherence (percentage of actual days / maximum number days, according to local practice) as 80% throughout the index hospital admission and the 7-day adherence at 70%, which has been included in the stop-go criteria. The TSC will meet every 6 months and at the end of month 15 (after 9 months of recruitment allowing 1 month processing time).

**Table 1: Internal pilot feasibility assessment at 9 months**

| Progression criteria                         | Red                                       | Amber        | Green  |
|----------------------------------------------|-------------------------------------------|--------------|--------|
| % Threshold                                  | <70                                       | 70 – 99.9%   | ≥100   |
| Trial recruitment (of eligible participants) | <17.9%                                    | 17.9 – 25.4% | ≥25.5% |
| Recruitment rate / site / month              | <7                                        | 7 – 9        | ≥10    |
| Number of sites opened                       | <25                                       | 25 - 35      | ≥36    |
| Total number of participants recruited       | <1100                                     | 1100 – 1570  | ≥1571  |
| Adherence                                    | <80% inpatient
<70% at 7-day follow-up |              |        |

## 4. PARTICIPANT ENTRY

### 4.1. INCLUSION CRITERIA

- Adults ( $\geq 18$  years)
- Participants undergoing elective surgery; risk assessed as requiring EDPTP\*\*

\*\* Participants are deemed to require extended duration thromboprophylaxis measures as per local policy in line with NICE [NG89] guidelines.

Examples of procedures from which patients are at highest-risk of VTE include (but are not limited to) (30, 31): orthopaedic surgery (total hip replacement, total knee replacement, colorectal surgery (colectomy, splenectomy), upper gastrointestinal surgery (oesophagectomy, gastrectomy), urological surgery (cystectomy, nephrectomy), and gynaecological oncology surgery (radical hysterectomy, radical trachelectomy).

### 4.2. EXCLUSION CRITERIA

- Contraindications to EDPTP or GCS
- Individuals requiring therapeutic anticoagulation\* e.g., anticoagulation for previous DVT
- Known thrombophilia or thrombogenic disorder

*\*antiplatelet therapy e.g. aspirin is not an exclusion*

### 4.3. WITHDRAWAL CRITERIA

Participants may discontinue study intervention for the following reasons:

- At the request of the participant.
- Adverse event/ Serious Adverse Event
- If the investigator considers that a participant's health will be compromised due to adverse events or concomitant illness that develop after entering the study.

The reason for participant withdrawal should be documented in the Study Completion CRF in REDCap. Participants that are withdrawn or lost to follow-up do not need to be replaced.

## **5. ASSESSMENT AND FOLLOW-UP**

### **5.1 ELIGIBILITY AND ASSESSMENT**

This trial will take place in approximately 36 to 50 NHS and non NHS sites offering day case and short stay surgical services. Patients from a variety of surgical specialties will be included in this pragmatic trial.

Trained members of the research team will identify eligible participants utilising the scheduling lists for the relevant surgical procedures, these can be easily generated at each site. Furthermore, when patients are being scheduled for intervention, potential participants will be informed about the trial by the clinician involved in listing them for their procedure.

The study will be advertised by posters and leaflets placed in clinical areas and on social media and websites.

Members of the research team will contact potential participants and inquire if they would be willing to be involved in clinical research and interested in receiving the Participant Information Sheet (via post or email). This will be supplemented by information available on the trial website, including information videos and infographics.

Prior to contact, a medical records review will be undertaken to ensure eligibility.

The reasons for non-inclusion will be logged pseudoanonymously along with a minimum data set of age, gender and reason for exclusion. The pseudoanonymised

screening logs will be transferred to the Trial Coordinating Centre for the purposes of monitoring recruitment.

NIHR INCLUDE Guidance (31) was thoroughly consulted during development of the GRACE trial. The eligibility criteria and recruitment strategy have been designed to minimise potential underserving of patient groups. The need for therapeutic anticoagulation or having a thrombophilia, the main exclusion criteria, are not known to be associated with underserving of any groups by demographic, social, or health status factors with exception of atrial fibrillation (an indication for anticoagulation) having a higher prevalence with increasing age (33). However, we do not believe that this increasing prevalence will be sufficient to cause underserving of this population (33) given the increasing prevalence of osteoarthritis with age (the main clinical indication for hip and knee replacement) and malignancy (clinical indication for colectomy, nephrectomy, radical hysterectomy).

To ensure the trial recruits participants in which their first language is not English, we have costed for professional translation of the participant information sheet and informed consent documentation.

On a broader level, all hospitals will be included with varying levels of VTE risk assessment compliance rates to reflect real-world practice. We have also reviewed UK Index of Multiple Deprivation and will ensure recruitment sites will be representative.

Hence, we believe that the trial has been designed and with the aim to deliver it in a way that is acceptable and feasible to a broad (and representative) range of people who will be undergoing surgical procedures that require extended duration thromboprophylaxis.

## 5.1.1. RANDOMISATION

The secure web-based randomisation element of the Research Electronic Data Capture (REDCap) database will be used to randomly allocate consenting participants. Trained staff, who are listed on the delegation log, will confirm eligibility before proceeding to randomisation. The randomisation result will be available immediately.

Stratification will be built into this randomisation element by centre and type of surgery.

Individual participants will be randomised in a 1:1 fashion to one of two thromboprophylaxis strategies:

1. EDPTP\* in addition to GCS (control arm), or
2. EDPTP alone (intervention arm)

\*EDPTP includes any anti-thrombotic agent prescribed at a prophylactic dose for prevention of VTE, including low-molecular weight heparin (LMWH), Directly acting Oral AntiCoagulants (DOACs), or antiplatelet therapy.

## 5.1.2. INTERVENTION

Participants randomised to the intervention arm will receive EDPTP alone (no GCS during the admission).

Extended duration pharmacological thromboprophylaxis is the practice of prescribing the thromboprophylaxis for a duration after hospital discharge. Prevention of DVT is a licenced indication and recommended by NICE guidelines [NG89] for several Low molecular weight heparins (LMWH) such as Tinzaparin, Enoxaparin, or Direct oral anticoagulants (DOACs) such as Rivaroxaban, Apixaban. Aspirin is an antiplatelet medication that reduces platelet function with a variety of clinical indications. The use of aspirin as DVT prophylaxis in orthopaedic surgery is also recommended by NICE [NG89](17). Prophylactic-dose thromboprophylaxis is prescribed at a lower dose in

comparison to clinical indications for therapeutic anticoagulation, such as in the treatment of diagnosed DVT or PE.

### **5.1.3. CONTROL**

Participants randomised to the control arm will receive both EDPTP post discharge and GCS for a period of time as per locally policy which may vary between Trusts.

GCS are elastic stockings worn on the lower limbs, often referred to by one of the brand names ThromboEmbolic Deterrent (TED®) stockings. They provide low pressure compression with the intended benefit to reduce the risk of VTE. Either below-knee or above-knee compression stockings may be used. The duration of stocking use should be as per local policy for example, until ambulant, discharge or post discharge.

The range of EDPTP available for the EDPTP and GCS stockings (the control group) will be the same as for the EDPTP alone group. As above agents commonly used include LMWH e.g., Tinzaparin, Enoxaparin, or DOACs e.g., Rivaroxaban, Apixaban. Prophylactic-dose thromboprophylaxis is prescribed at a lower dose in comparison to clinical indications for therapeutic anticoagulation, such as in the treatment of diagnosed DVT or PE. Extended duration pharmacological thromboprophylaxis is the practice of prescribing the thromboprophylaxis for a duration after hospital discharge. Prevention of DVT is a licenced indication for several LMWH and DOACs and recommended by NICE guidelines [NG89]. Aspirin is an antiplatelet medication that reduces platelet function with a variety of clinical indications. The use of aspirin as DVT prophylaxis in orthopaedic surgery is also recommended by NICE [NG89](17).

## **5.2 INFORMED CONSENT**

Informed consent for enrolment will be ascertained from potential participants utilising either of the following approaches:

1. Prior to the day of procedure, through in person pre-assessment clinics or remotely utilising online meetings or telephone consultation.
2. On the day of, but prior to, their procedure through in person consultation.

Participants will have already received the Participant Information Sheet, and the Informed Consent form for reference, ahead of being approached for consent. Trained members of the research team will gain informed consent from participants.

Consent will be obtained in writing, verbally or electronically via econsent.

Any interested participants wishing to econsent will be emailed a link to the econsent form within the REDCAP database where they will be able to provide consent. RECAP provides an audit trail and signatures are attributed to the person completing this. The participant will be sent a copy of their consent form via email.

Participants who prefer to provide consent via telephone will be sent the information sheet and consent form for review via email. The research nurse/practitioner will then read off each statement on the consent form and ask the participant to confirm agreement with each statement. The researcher should initial the boxes with a note indicating that subjects had agreed to each point on the ICF. The research nurse/practitioner will then sign-off on the consent form to state that consent has been provided verbally over the telephone. The participant will be sent a copy of their consent form via email/post.

Prior to the surgical procedure, all participants will be provided with a leaflet which explains the signs and symptoms of developing a blood clot. Although VTE outcome will be assessed at 7, 21 to 35 days and 90-days post-procedure, participants will be advised to visit the emergency department if they suspect they have developed a blood clot (and not to wait for the study team to make contact).

Prior to the procedure, the following information will be collected from the patient and medical records:

- Baseline demographic information
- Name of surgical procedure
- Previous medical history and current medication

## **5.3 FOLLOW-UP**

Participants will be contacted by the central study team at days 7, between 21 and 35 days, and 90 days to obtain follow up data. The follow-up will be conducted either by telephone, SMS, web or written depending on participant preference.

Participants will undergo a bilateral full lower limb (groin to ankle) deep venous thrombosis scan at 21- 35 days post-intervention to identify asymptomatic DVT, this is timed to capture the peak onset of events which is at 3 weeks (34). Reasonable travel expenses will be reimbursed for this visit.

### **Day 7 post procedure**

Day 7 post procedure (data collected via telephone or online survey [link to survey sent via email or SMS])

- VTE outcome (participants will be asked to report on whether or not they have been diagnosed with a DVT or PE within the past 7-days)
- Adverse events associated with GCS will be captured (for those enrolled in the control arm)
- Participant reported adherence to GCS (for those enrolled in the control arm)
- Adherence to EDPTP

## **Day 21 to 35 post procedure**

Day 21 to 35 post procedure (data collected via telephone or online survey [link to survey sent via email or SMS])

- VTE outcome (participants will be asked to report on whether or not they have been diagnosed with a DVT or PE since last contact)
- Adverse events associated with GCS will be captured (for those enrolled in the control arm)
- Participant reported adherence to GCS (for those enrolled in the control arm)
- Adherence to EDPTP
- Participants will also undergo a bilateral full lower limb (groin to ankle) deep venous thrombosis scan at 21- 35 days post-intervention to identify asymptomatic DVT

## **Day 90 post procedure**

Day 90 post procedure (data collected via telephone or online survey [link to survey sent via email or SMS])

- VTE outcome (participants will be asked to report on whether or not they have been diagnosed with a DVT or PE since last contact)
- Adverse events associated with GCS will be captured (for those enrolled in the control arm)
- Participant reported adherence (for those enrolled in the control arm)
- Adherence to EDPTP

If the patient reports a VTE within the trial period that was not captured on the 21-to-35-day ultrasound we will request verification that imaging has confirmed the diagnosis.

Mortality within the 90-day follow-up period will also be captured. Follow-up data will be assessed blindly.

As this is a pragmatic trial, we will look to measure adherence and ensure it is reasonable but not attempt to introduce new interventions to increase adherence above what would be reasonably expected. We consulted the patient representatives, who have lived experience of wearing GCS, to establish how best to monitor adherence without unduly promoting increased adherence within the trial. Telephone consultation supplemented with remote messages by smart phone with electronic response to establish adherence was preferred. This was also reflected in wider PPI undertaken for other VTE prevention studies.

Any incidental findings identified during the study from the lower limb VTE ultrasound or self reported follow-up will be reported the clinical care team for any required treatment and follow-up.

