## 1. INTRODUCTION

### 1.1. BACKGROUND

Hospital-acquired thrombosis (HAT) is defined as any venous thromboembolism (VTE) during admission and within 90 days of hospital discharge (1), and is a term that encompasses both deep vein thrombosis (DVT) and pulmonary embolism (PE). It is estimated that as many as 60% of all VTE cases are hospital related (2). HAT represents a significant cause of preventable mortality, with around 60.4 deaths from VTE per 100,000 hospital admissions reported in the year 2020-2021 within the NHS (1) – equivalent to around 12,300 people dying each year from hospital-caused VTE, which is 10-fold higher than the number dying from road traffic accidents. The UK annual VTE-related mortality prior to implementation of a national programme of thromboprophylaxis, was estimated to be up to 32,000 fatalities, with associated costs as high as £640 million per annum (3).

VTE is a significant cause of long-term disability with subsequent societal and economic consequences (4). Morbidity following a DVT is substantial, with as many as 50% of patients developing post thrombotic syndrome (PTS) (5), characterised by troubling chronic leg pain, oedema, and venous skin changes (6). Crucially, the severity of chronic venous disease is much worse in those with PTS in comparison to primary venous disease and the rate of venous ulceration is as high as 29% (7). Those with PTS have a significantly worse quality of life, which is comparable to those with cancer and congestive heart failure (8, 9). Furthermore, PE is associated in some with life-long functional, physiological and psychological harm (10, 11). Ultimately, PE can cause death during the index event and in an estimated 2% can be complicated by chronic thromboembolic pulmonary hypertension, resulting in chronic pulmonary hypertension and heart failure (12, 13). Persistent cardiac insufficiency have been reported in as many as 13.2% of PE cases (11).

Surgery is a significant risk factor for VTE, with those undergoing lower extremity orthopaedic operations, major oncological surgery or pelvic surgery being at the highest risk (14, 15). Previous studies report the risk of untreated high-risk surgical

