## **2.1 PRIMARY OUTCOME**

The primary outcome is imaging-confirmed lower limb DVT with or without symptoms, or PE with symptoms, occurring up to 90 days post-surgery.

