## 6.2 Statistical analyses

Statistical analysis will be governed by a comprehensive SAP written by the study statistician and agreed by the independent Trial Steering Committee (TSC) and independent Data Monitoring Committee (iDMC) before any unblinded data is seen.

Main analysis will be according to intention-to-treat principle and will compare rates of VTE at 90 days, adjusting for any pre-specified strongly prognostic baseline covariates using a mixed effects logistic regression with study site as a random effect and pre-specified baseline covariates strongly related to outcome being used to adjust the estimated treatment effect. Primary outcome will be VTE at any time up to 90 days. The findings will be assessed for robustness against any missing data, first using multiple imputation assuming this data is missing at random and, if appropriate and the data permits, further sensitivity analyses will be attempted under any plausible missing data mechanisms not missing at random. In particular, since for non-inferiority designs, in which the null hypothesis is that the randomised groups differ, the intention-to-treat analysis may not be the most conservative, and so we will conduct a suitably specified Per Protocol analysis (defined by adherence to study protocol) as a supporting analysis to the main ITT analysis. We will also include a time to event specification (a Fine & Gray) model of the primary endpoint to check on the influence of any competing risk of death (expected to be a rare event at  $\sim 1\%$  overall). Secondary

outcomes will be analysed in a similar fashion with generalised linear models appropriate to the distribution of the outcome. Safety data will be summarised descriptively. An additional sensitivity analysis of NHS-only patients (including patients referred by their GPs to non-NHS sites) will be conducted to ensure generalisability to a NHS population.

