## Appendix 1. Summary of investigations, treatment and assessments

| Assessment                                                                        | Days of assessment     |                      |   |          |    |
|-----------------------------------------------------------------------------------|------------------------|----------------------|---|----------|----|
|                                                                                   | Pre-surgical procedure | 0 (Day of procedure) | 7 | 21 to 35 | 90 |
| Inclusion/Exclusion                                                               | X                      | X                    |   |          |    |
| Informed consent                                                      | X                      |                      |   |          |    |
| Screening assessments                                                             | X                      |                      |   |          |    |
| Demographics                                                          |                        | X                    |   |          |    |
| Medical history (including concurrent medications)                    |                        | X                    | X | X        |    |
| Provision of leaflet explaining the signs and symptoms of developing a blood clot | X                      |                      |   |          |    |
| Provision of stockings*                                                           |                        | X                    |   |          |    |
| VTE outcome (self-reported)                                                       |                        |                      | X | X        | X  |
| A full lower limb deep venous thrombosis scan                                     |                        |                      |   | X        |    |
| Adverse Events Assessment*                                                        |                        |                      | X | X        | X  |
| Adherence to GCS*                                                                 |                        |                      | X | X        | X  |
| Adherence to EDPTP                                                                |                        |                      | X | X        | X  |

\*Patients randomised to the control arm only

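### A PE that kills before the participant can report it has no described route into the VTE endpoint, and deaths are recorded without cause

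*Protocol*

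**What the plan says.** Protocol section 2.1 defines the endpoint: "The primary outcome is imaging-confirmed lower limb DVT with or without symptoms, or PE with symptoms, occurring up to 90 days post-surgery". It does not mention PE diagnosed at death.

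Section 5.3 describes how VTE is found. There is one bilateral leg scan at days 21 to 35. Otherwise there are contacts at day 7, days 21 to 35 and day 90; at the last two, "participants will be asked to report on whether or not they have been diagnosed with a DVT or PE since last contact", and day 7 asks the same about the preceding week. Appendix 1 gives this item a label that begins "VTE outcome (self-reported". Verification is set out under Day 90: "If the patient reports a VTE within the trial period that was not captured on the 21-to-35-day ultrasound we will request verification" that imaging confirmed the diagnosis.

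On deaths, the same section says: "Mortality within the 90-day follow-up period will also be captured". Mortality is a secondary outcome in section 2.2. Cause of death is not mentioned there or elsewhere in the protocol.

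Section 6.2 makes a mixed effects logistic regression the main analysis. It adds a Fine and Gray model "to check on the influence of any competing risk of death", with deaths expected at about 1% overall.

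**The concern.** Each described step for a VTE not found on the scan depends on a living participant who answers a contact. Someone who dies of PE between contacts cannot take the first step. A PE identified only at post-mortem or from the certificate also does not fit a step that asks for imaging.

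The trial tests whether a preventive measure can be left out, and section 1.1 motivates it partly by deaths: "HAT represents a significant cause of preventable mortality". The sponsor's own systematic review (section 1.2) pooled VTE-related mortality as an outcome distinct from DVT and PE. If fatal PE can drop out of the VTE count and reappear only as an unclassified death, the endpoint omits the most severe failure of prophylaxis. The trial also could not say afterwards whether such deaths differed between arms. An SAP may set rules for classifying deaths, but it cannot supply a cause that was never collected.

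**Working it through.** **1. Tracing a fatal PE through the protocol**

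- *Scan (5.3):* reached only if the participant is alive at days 21 to 35, and it images the legs.
- *Self-report (5.3, Appendix 1):* possible only if the PE was diagnosed and reported before death.
- *Adverse events (7.2, 7.2.1, Appendix 1):* recording is limited to stocking-related events, and the assessment is scheduled in the control arm only. A fatal PE in the EDPTP-alone arm is not covered.
- *SAE form (7.1, 7.2.2):* death meets the definition, but nothing links the form to the VTE endpoint or to masked classification.
- *Medical records (9.1):* permitted as source data, but no check after a death is required.

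**2. Reproducing the plan's figures (6.1)**

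Inputs: 8% in both arms, margin 2 points, one-sided 2.5%, 90% power.

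- n per arm = (1.960 + 1.282)² × 2 × 0.08 × 0.92 / 0.02² ≈ 3,867, so 7,734 in total (stated 7,736).
- 8,264 / 0.96 = 8,608.3 (stated 8,608). The group sequential inflation to 8,264 is taken as given.

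**3. Expected counts among 8,608**

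- PE at the stated 0.05% to 0.11%: 4.3 to 9.5 in total.
- Deaths at about 1%: 86, or 43 per arm.

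**4. Effect on the non-inferiority test**

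With 4,132 analysed per arm (8,264 / 2), SE = √(2 × 0.08 × 0.92 / 4,132) = 0.597 points. The margin equals 0.02 × 4,132 ≈ 83 events per arm. At the final threshold of 2.00, the chance of declaring non-inferiority when the rates are equal is Φ(2.0/0.597 − 2.00) = 91.2%.

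The fatal share of PE and the ratio between arms are assumptions, since the protocol gives neither. The last column is the chance of declaring non-inferiority if the omitted events were counted on top of an equal 8%, using unpooled variances.

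| Assumed fatal PE, control | Ratio without stockings | Events (control v alone) | Hidden difference | Chance if counted |
|---|---|---|---|---|
| 0.11% (every PE fatal and missed) | 1 | 4.5 v 4.5 | 0 | 90.8% |
| 0.11% | 2 | 4.5 v 9.1 | 0.11 points (0.18 SE) | 87.2% |
| 0.11% | 3 | 4.5 v 13.6 | 0.22 points (0.37 SE) | 82.8% |
| 0.10% (a tenth of deaths) | 2 | 4.1 v 8.3 | 0.10 points (0.17 SE) | 87.6% |
| 0.10% | 3 | 4.1 v 12.4 | 0.20 points (0.34 SE) | 83.7% |

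A simple extreme: 5 v 0 in 4,304 per arm is 5/4,304 = 0.12 points, about 6% of the margin.

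**5. Can all-cause mortality stand in?**

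With 4,304 per arm, two-sided 5%:

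- 1.00% v 1.11%: difference 0.11 points, SE = √((0.01 × 0.99 + 0.0111 × 0.9889)/4,304) = 0.220 points. Power = Φ(0.50 − 1.96) ≈ 7%.
- 1.0% v 1.5%: SE = 0.239 points. Power = Φ(2.09 − 1.96) ≈ 55%.

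**The case against.** A reader might infer that a fatal PE can never become a primary event. The protocol does not say so. A PE imaged before death meets section 2.1 on any reading, and a confirmed VTE reported at an earlier contact already counts. Section 2.1 leaves open whether the imaging requirement governs PE at all, and the check in 5.3 is attached to self-reports without excluding other sources. Records are allowed as source data (9.1) and death falls within the SAE definition (7.1). All of this stands. What remains is that no passage requires anyone to use these sources to classify a death.

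A reader might also infer that the main analysis treats fatal PE as a competing death. It does not: only the supporting Fine and Gray model brings in competing risk. Section 6.2 does not say how a death without recorded VTE enters the logistic model. Coding of that kind may be settled in the SAP, which is not shown.

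Nor do the documents show that the harm is hidden or the result biased. Deaths are counted by arm as a secondary outcome, and section 6.4 lets the iDMC act on an excess of events in the intervention group. Equal omission in both arms leaves the risk difference unchanged, and the sponsor's review found no significant difference in VTE-related mortality.

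Finally, the 60.4 VTE deaths per 100,000 admissions in section 1.1 would give 5.2 deaths in 8,608. Set against 4.3 to 9.5 PEs, that implies 55% to 121% fatality. The two figures describe different populations and cannot be combined to claim that missed fatal PE would rival all PE counted.

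**Conclusion.** The point holds as a gap in ascertainment and classification. The described route for VTE outside the scan starts with the participant's own report, deaths carry no cause, and a PE first recognised at or after death is not provided for. Without a cause, the Fine and Gray model would place such a death under competing risk although it is a failure of prophylaxis.

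The numerical effect on the primary test is small. It is about 0.1 to 0.2 points of a 2-point margin under assumed doubling or tripling of fatal PE at or near the protocol's upper PE rate, and nil if the arms are equal. Bias towards non-inferiority requires an excess of fatal PE without stockings, which the documents do not show. Sample size is not in question.

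The real loss is in what the endpoint means and what can be said about safety. At the stated 1% mortality, an all-cause comparison would almost never reveal a PE-specific excess of the size considered here, and a handful of fatal PEs needs to be visible as such. This is a worthwhile, inexpensive improvement, not a fault that undermines the design.

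**What to change.** - **Section 5.3:** for every death to day 90, record from the hospital record, death certificate or post-mortem whether it was VTE-related, classified by someone masked to allocation.
- **Section 2.1:** state whether the imaging requirement applies to PE, and how PE diagnosed at death is classified.
- **Section 2.2:** add VTE-related death as a secondary outcome, reported by arm to the iDMC.
- **Section 6.2:** add a sensitivity analysis of the primary outcome that counts VTE-related death as a VTE event. In the Fine and Gray model, treat only non-VTE death as the competing event.

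Adding a secondary outcome and a sensitivity analysis avoids adding VTE-related death to the primary composite during the trial. The cost is protocol wording, one CRF field and record retrieval for about 86 deaths that are already being captured. No extra visit or procedure is needed.
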